2. STUDY DESIGN
3. STUDY VISIT SCHEDULE
4. REFERENCES
5. **BACKGROUND AND RATIONALE**

Mixed states in bipolar disorder have long been recognized. Over a century ago, Weygandt argued that mixed states were the most common presentations in manic-depressive illness [1], and later Kraepelin agreed [2]. While Kraepelin identified pure depression and pure mania, he described 6 different mixed states, which he considered more prevalent than pure mood states [2].

In DSM-IV, the definition of a mixed episode was narrowed, compared to previous definitions, so as to require full criteria for both mania and depression. This was not primarily based on empirical grounds, but rather, according to some members of the DSM-IV committee [3], so as to compensate for expansion of the bipolar diagnosis in other areas (eg., inclusion of type II and rapid cycling definitions).

In the last decade, a number of studies have suggested that the previous broader definitions of mixed states may have diagnostic validity and therapeutic utility. Empirical studies support the possible validity of definitions of mixed state in which manic episode criteria are met with two or more depressive criteria (dysphoric mania) [4]. Using this definition, for instance, one study demonstrated greater treatment response with valproate than with lithium [5]. Other clinical studies suggest that a mixed state may be present when major depressive episode criteria are met with at least one manic criterion (such as racing thoughts) [6, 7]. In those clinical studies, such mixed states appeared less responsive to antidepressants and more responsive to adjunctive mood stabilizers [8].

Using the narrow DSM-IV criteria, less than 10% of episodes in patients with bipolar disorder would meet criteria for a mixed episode. Using broader mixed states criteria incorporating the clinical pictures of dysphoric mania and agitated depression, similar data suggest that about 50% of episodes in bipolar disorder would be diagnosable as mixed states. One study found that only 54% of 143 broadly defined mixed states (using Kraepelinian definitions) met DSM-III-R criteria for the mixed episode [9].

It should be noted that this study of the depressive mixed state differs from a study of “agitated depression”. The concept of agitated depression does not have a consensus definition; usually it entails a major depressive episode with at least psychomotor agitation. The depressive mixed state, on the other hand, is defined as more than simply psychomotor agitation along with depression: there must also be one or two other manic symptoms (depending on the definition). Three more manic symptoms would define the condition as a DSM-IV mixed episode. Thus the depressive mixed state is a subthreshold DSM-IV mixed episode.

Studies suggest that the majority of persons with a depressive mixed state have bipolar disorder type II, but a substantial group will also have unipolar depression, according to DSM-IV criteria [7].

Ziprasidone appeared to be especially effective in treating manic patients who met DSM-IV criteria for a mixed episode in its registration trials. Due to unequal sample sizes in randomized groups, however, only 4 patients were randomized to placebo among those with mixed episodes (Pfizer, data on file). Nonetheless, those pilot data, along with the biochemical effects of ziprasidone on serotonergic neurotransmission, support the potentially selective utility of this agent in those with a mixture of manic and depressive symptoms.

The purpose of the proposed study is to examine the efficacy of ziprasidone for the depressive mixed state in patients with bipolar or unipolar depression. This will be the first double-blind RCT in the depressive mixed state. Pfizer is sponsoring this study.

.

## STUDY OBJECTIVES

The primary outcome of this study is to determine if ziprasidone is effective for the depressive mixed state in bipolar and unipolar depression.

1. **STUDY DESIGN**

This will be a four-site, block randomized (1:1 ratio) double-blind, placebo-controlled prospective study in which 100 patients will be enrolled. Patients will be randomized to ziprasidone or placebo in the 6 week acute phase of the study. Randomization will be stratified by three factors: subtype of depressive disorder (bipolar type II vs. unipolar), presence or absence of rapid cycling and duration of current MDE (< vs. > 3 months). The primary outcome measure will be change from baseline Montgomery-Asberg Depression Rating Scale scores in the acute phase. Enrollment will occur over 12 months.

###### STUDY POPULATION

#### Number of Subjects

We plan on enrolling 100 subjects overall, 25 subjects at the Tufts Medical Center site. A full power analysis is provided in section VIIIA.

#### Subject Recruitment

In order to avoid any appearance of coercion by the treating clinician, study coordinator [name] will always conduct initial presentation of the study.

#### Inclusion Criteria

1. Age 18-65
2. Diagnosis of Bipolar Disorder Type II, or unipolar major depressive disorder
3. If female, nonpregnant/nonlactating
4. If a sexually active female of reproductive potential, must be using adequate contraception (i.e., oral contraceptives, barrier protection, or prior tubal ligation)
5. Currently meets DSM-IV criteria for a major depressive episode, and presence of 2 or 3 DSM-IV manic criteria
6. All other baseline psychotropic drugs will be allowed to be continued unchanged. However, if antidepressant use had been initiated in the previous 2 months, or was thought to be contributing to the depressive mixed state, then antidepressant medications would be discontinued 2 weeks (5 weeks for fluoxetine) before initiating the study.
7. Decisional capacity will be assessed by [name] utilizing the standard psychiatric approach to assessing capacity:

- Factual understanding
- Appreciation of available options
- Rational thought process
- Communication of awareness

Please note that the subjects invited to participate are not psychotic, and do not have cognitive impairment.

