#### Exclusion Criteria

1. Substance abuse or dependence in the previous month or positive urine drug screen at screening or relapse during study to substance abuse (meeting DSM-IV criteria).
2. Medically unstable as judged by study investigators
3. Lack of capacity to provide informed, written, consent to investigators
4. Previous intolerance to ziprasidone or current use of ziprasidone at study baseline or within 3 months of study entry.
5. Serious suicidality as evidenced by score of 3 or greater on suicide item of MADRS
6. Previous diagnosed cardiac arrhythmias
7. Current psychotic major depressive episode
8. History of potentially lethal suicide attempt

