### Dosage Regimen

The once-daily total daily dose will be 80-160 mg/d of ziprasidone. Dosing will begin at 20 mg BID with a flexible dose escalation strategy based on target symptoms and tolerability, with a target dose range of 80-160 mg/d. Dose escalations will occur by increments of 20-40 mg weekly.

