### Visit-Specific Treatment and Evaluation Sequence

Visits will be planned to occur at the screening visit and weeks 0, 1, 2, 3, 4, 5, 6. Research scales will be administered at each visit. For a detailed description of which scales are administered per visit, please see “XIV. Study Visit Schedule” on page 21. No research procedures will be performed without a patient first signing an informed consent. Laboratory tests, consisting of CBC with differential, biochemistry profile, ECG and urine pregnancy test, will be conducted prior to the acute phase, prior to the continuation phase, and at study termination. Physical examination and vital signs will be assessed at study entry and termination visits. Patient termination will occur if the patient experiences a worsening of MADRS scores greater than 30% above the baseline score in two successive visits or if MRS > 20 in two successive visits, or based on clinician judgment or patient preference.

1. Concomitant Medication and Therapy

All allowed concomitant medications will be unchanged throughout the study.

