### Randomization Method

Randomization will occur with randomly generated computer lists held at the Duke site. All patients will be stratified by the following characteristics in block randomization:

Subtype of depressive disorder (bipolar type II vs. unipolar), presence or absence of rapid cycling, and duration of current MDE (< vs. > 3 months). These features may be unequally distributed in a small (<50) randomized study and could lead to high placebo response if type II, rapid cycling, or short duration episodes are overrepresented in the placebo group. Stratification will ensure control of these factors.

1. Outcome Measures and Planned Analyses

The a priori primary outcome measure will be change from baseline in MADRS scores in the acute phase. A priori secondary measures will be change from baseline in HAM-A, MRS, and other scores. The primary analysis for the acute phase between group effect size (for ziprasidone vs. placebo) will be obtained by unpaired t-test comparison and by mixed effects regression modeling. A priori subgroup analysis in rapid cyclers versus nonrapid cyclers, unipolar vs. bipolar subtypes, and shorter versus longer duration episodes, is also planned.

1. Definition of Evaluable Subject (Safety and Efficacy)

Subjects will be defined as able to be evaluated by two methods. The primary method will be an intent-to-treat analysis, including those who discontinue drug due to lack of efficacy or due to side effects. The secondary method will be completer analysis.

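### Entry sets no MRS limit, yet MRS > 20 at two successive visits forces termination: a patient who enters above 20 and stays there is stopped by Week 2 without worsening

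*Protocol*

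**What the plan says.** **Entry.** Inclusion Criteria, item 5, reads "Currently meets DSM-IV criteria for a major depressive episode, and presence of 2 or 3 DSM-IV manic criteria". Item 2 restricts the diagnosis to bipolar II or unipolar depression, and Background and Rationale describes the target condition in these terms: "Thus the depressive mixed state is a subthreshold DSM-IV mixed episode". None of the eight exclusions mentions the MRS. One of them does set a limit on a rating-scale item: "Serious suicidality as evidenced by score of 3 or greater on suicide item of MADRS".

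**Stopping.** Visit-Specific Treatment and Evaluation Sequence says that termination will occur on "worsening of MADRS scores greater than 30% above the baseline score in two successive visits" "or if MRS > 20 in two successive visits". Study Discontinuation/Termination repeats both rules as reasons for which patients will be discontinued, and adds a stop for worsening suicidal ideation based on the MADRS suicide item. The MRS rule refers to no baseline value in either place.

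**Visits.** "Visits will be planned to occur at the screening visit and weeks 0, 1, 2, 3, 4, 5, 6". The Study Visit Schedule marks both MRS and MADRS at every one of these visits, including screening and Week 0.

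**Analysis set.** "The primary method will be an intent-to-treat analysis, including those who discontinue drug due to lack of efficacy or due to side effects". A completer analysis is secondary.

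**The concern.** A count of manic criteria is not a severity score. It restrains the MRS total but does not cap it. The trial may therefore randomise someone who is already above the level at which its own rules require withdrawal. Such a patient would be removed for being what they were at entry, not for anything that happened on treatment.

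What is lost is the rest of that patient's blinded follow-up, which is most of the planned MADRS course. The patient also leaves the completer set. The stop would come while the dose is still being raised: treatment starts at 20 mg BID and "Dose escalations will occur by increments of 20-40 mg weekly". There is an avoidable burden too, since a patient goes through randomisation and possible placebo treatment only to meet a stopping rule that could have been checked beforehand.

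An analysis plan cannot repair this, because eligibility and withdrawal rules belong to the protocol.

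**Working it through.** No figure in the protocol bears on this point, so there is none to reproduce. The check compares the entry and stopping rules, then applies the MRS rule to the visit schedule.

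**Step 1: the three score-based stops side by side.**

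| Stop | Relative to baseline? | Matching limit at entry? | Can an unchanged patient meet it? |
| --- | --- | --- | --- |
| MADRS, more than 30% worse | Yes | Not needed | No |
| MADRS suicide item, cut-off 3 | No, but worded as worsening | Yes, 3 or greater is excluded | No |
| MRS > 20 | No | None | Yes, if entry MRS > 20 |

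Only the MRS stop has neither safeguard.

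**Step 2: when the rule is met.** The rule is met at the second of two consecutive visits with MRS > 20. The courses below are illustrative; their MRS values are assumed.

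| MRS course from Week 0 | Only post-baseline visits count | Week 0 also counts |
| --- | --- | --- |
| Constant 19 or 20 | Never | Never |
| Constant 21 or 25 | Week 2 | Week 1 |
| 28, 24, 21, 18 (improving) | Week 2 | Week 1 |

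The improving patient has fallen by 28 − 21 = 7 points by Week 2 and is still stopped. In the assumed course, the Week 3 value of 18 would have been below the threshold.

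The protocol does not say which visits count. Since it lists screening as a visit, a literal reading would also allow the stop at Week 0, before any dose, for a patient above 20 at both screening and Week 0. The post-baseline reading is the most consistent one, because the MADRS rule in the same sentence can only use visits after baseline. *By Week 2* holds under every reading.

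**Step 3: MADRS ratings available.** Post-baseline ratings are planned at Weeks 1 to 6, which makes 6. A Week 2 stop leaves 2 of 6 and a Week 1 stop leaves 1 of 6, so the patient supplies at most 2 of 6.

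**Step 4: the rule after correction.** With entry restricted to MRS ≤ 20 at Week 0 and only later visits counted, any qualifying value above 20 is necessarily a rise from Week 0. An unchanged or improving patient can then never meet the stop.

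**The case against.** **The affected group may be empty.** Entry is confined to bipolar II or unipolar patients with two or three manic criteria, checked by structured interview, in a condition the protocol calls subthreshold. Whether such a patient can score above 20 depends on the range and item scoring of the MRS, which the protocol does not give. This stands, and it is the main reason for the low severity. It does not close the gap, because the protocol contains nothing that excludes such a patient.

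**An absolute ceiling may be deliberate.** Two visits at a high manic score could justify leaving a placebo-controlled phase whether or not the patient has changed, and the protocol does not word the MRS rule as worsening. That is a fair reading. But if a score above 20 makes continued participation unsuitable, the same reasoning says the patient should not be randomised.

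**Stronger conclusions a reader might draw are not supported.**

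- *That the rule biases the primary comparison.* Whether a patient stays above 20 could depend on the arm, but this is true of every symptom-based stop, including the MADRS stop and clinician judgement. It would remain to some degree after an entry limit. It is not specific to the missing limit.
- *That the effect on the mean difference or its precision can be quantified.* Any figure would need assumed counts, an assumed loss of improvement and an assumed handling of last ratings. The protocol supplies none of these. It also plans mixed effects regression, which can use the Week 1 and Week 2 ratings.
- *That these patients fall out of the primary analysis.* It is by intention to treat. Only their later ratings are missing.
- *That a Week 2 stop corresponds to a fixed share of the treatment course.* Escalation is flexible, depending on symptoms and tolerability, so a patient could still be on 40 mg/d in Week 2.
- *That the entry criterion and the stop contradict each other.* They can both be applied as written; they are just not aligned.

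**Conclusion.** The point holds as a low-severity inconsistency between eligibility and withdrawal. The protocol sets no MRS limit at entry and requires termination at an absolute MRS > 20. An eligible patient who enters above 20 and is still above 20 at Weeks 1 and 2 must therefore be stopped by Week 2 without having worsened, with at most 2 of 6 post-baseline MADRS ratings.

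The conclusion is conditional on such a patient being enrolled. The symptom-count criterion makes that uncommon. The number cannot be computed from the document and may be zero, so no claim is made about bias, power or dose exposure. The point is worth raising because the score needed to prevent the problem is already collected at Week 0.

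**What to change.** 1. Add to the Exclusion Criteria: *MRS total above 20 at Week 0, rated before randomisation.* This mirrors the existing suicide-item exclusion.
2. In both places where the stop appears (Visit-Specific Treatment and Evaluation Sequence; Study Discontinuation/Termination), word it as *MRS > 20 in two successive post-randomisation visits*. This also gives the four sites a single reading of which visits count.

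**Alternative, if the sponsor wants to keep high-MRS patients:** set no entry limit, but require a rise above the baseline MRS as well as MRS > 20 at the two visits. A patient constant at 25, or falling 28, 24, 21, would then continue. Clinician judgement and the stop for clinical worsening remain available for anyone who is unsafe to continue.

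**Cost.** The first option needs one check of a score already collected and one clarifying phrase in two sections. Its downside is that a few high-MRS patients are screened out of a trial of mixed states, and some of them might have fallen below 20 on treatment. The alternative avoids that, but keeps patients blinded, possibly on placebo, at a level the present rule treats as grounds for stopping. The sponsor should make that choice explicitly.

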#### Exclusion Criteria

1. Substance abuse or dependence in the previous month or positive urine drug screen at screening or relapse during study to substance abuse (meeting DSM-IV criteria).
2. Medically unstable as judged by study investigators
3. Lack of capacity to provide informed, written, consent to investigators
4. Previous intolerance to ziprasidone or current use of ziprasidone at study baseline or within 3 months of study entry.
5. Serious suicidality as evidenced by score of 3 or greater on suicide item of MADRS
6. Previous diagnosed cardiac arrhythmias
7. Current psychotic major depressive episode
8. History of potentially lethal suicide attempt

##### STUDY PROCEDURES

### Blinding and Controls

The study will be double blind and randomized. There will be two arms, ziprasidone and placebo, that will serve as comparators. All subjects will be offered the option of an open label courtesy trial of up to 8 weeks of treatment with ziprasidone at no charge upon their study conclusion. Subjects who do not complete the full 6-week double-blind trial will be eligible for the open courtesy trial after the baseline visit, given that they have been found eligible based on the inclusion and exclusion criteria.

### Dosage Regimen

The once-daily total daily dose will be 80-160 mg/d of ziprasidone. Dosing will begin at 20 mg BID with a flexible dose escalation strategy based on target symptoms and tolerability, with a target dose range of 80-160 mg/d. Dose escalations will occur by increments of 20-40 mg weekly.

### Visit-Specific Treatment and Evaluation Sequence

Visits will be planned to occur at the screening visit and weeks 0, 1, 2, 3, 4, 5, 6. Research scales will be administered at each visit. For a detailed description of which scales are administered per visit, please see “XIV. Study Visit Schedule” on page 21. No research procedures will be performed without a patient first signing an informed consent. Laboratory tests, consisting of CBC with differential, biochemistry profile, ECG and urine pregnancy test, will be conducted prior to the acute phase, prior to the continuation phase, and at study termination. Physical examination and vital signs will be assessed at study entry and termination visits. Patient termination will occur if the patient experiences a worsening of MADRS scores greater than 30% above the baseline score in two successive visits or if MRS > 20 in two successive visits, or based on clinician judgment or patient preference.

1. Concomitant Medication and Therapy

All allowed concomitant medications will be unchanged throughout the study.

###### STUDY MEDICATION

1. Description and Dispensing

All medications will be dispensed by licensed research pharmacies.

1. Storage

All study medications at the Cambridge Health Alliance site will be stored in a double-locked cabinet in the main hospital pharmacy offices, accessible only to the study investigator and dispensed by staff pharmacists.

###### CLINICAL ASSESSMENTS

1. Structured Clinical Interview for DSM-IV Axis I Disorders-Patient Edition (SCID) [10] - The SCID mood module for current major depressive and manic syndromes will be administered at screening to verify DSM-IV diagnosis
2. Montgomery Asberg Depression Rating Scale (MADRS) [11] - The MADRS is a standard antidepressant rating scale, which is most sensitive to core mood symptoms in bipolar depression.
3. Quick Inventory for Depressive Symptoms (QIDS) [12] - A16-item clinician rated depression scale similar to the MADRS but which focuses on atypical symptoms.
4. Mania Rating Scale from SADS-C (MRS) [13]- This is derived from the SADS and has been used in numerous clinical trials of mania
5. Hamilton Scale of Anxiety (HAM-A) [14]- 12 item assessment on a scale of 0-4 of anxious mood; mostly dealing with physical symptoms.
6. Quality of Life Enjoyment and Satisfaction Questionnaire (Q-LES-Q) [15]- A weekly comprehensive self-rated quality of life questionnaire which targets specific areas of physical health/activities, feelings, work, household duties, school/course work, leisure activities, social relations and general activities.
7. Scale to Assess Unawareness of Mental Disorder (SUMD) [16]–This is a validated reliable scale used in the DSM-IV field trials to assess insight (awareness of illness). Insight may improve with ziprasidone, which would be an important predictor of compliance and improved long-term clinical prognosis.
8. Drug Attitude Inventory (DAI) [17]– This is a patient self report of subjective attitude toward taking medications, and again correlates with compliance.
9. Clinical Global Impression for Bipolar Disorder (CGI-BP) [18]– This is also an NIMH-derived scale that allows for separate global assessments of depressive, manic, and prophylactic efficacy in bipolar disorder.
10. Global Assessment of Functioning (GAF) [19]– The GAF is a single item clinician-rated scale that indicates overall level of psychosocial function during a specific period.
11. Longitudinal Internal Follow-up Evaluation: Range of Impairment of Functioning Tool (LIFE-RIFT) [20]- A scale to assess social/occupational functioning.
12. Systematic Assessment for Treatment Emergent Events – General Inquiry
13. Barnes Akathisia Scale (BAS) [21]- A 4-item clinician rated scale to assess symptoms of akathisia.
14. Simpson-Angus Scale for extrapyramidal symptoms (SAS) - A 10-item clinician rated scale to assess the presence and severity of extrapyramidal symptoms.
15. The structured Family History Screen (FHS) [22]- A brief family history in a structured manner to collect lifetime family psychiatric history and verify subject symptoms and treatment, to be completed by the subject.
16. The Temperament and Affective Disorders Questionnaire (TEMPS-A) [23]- 110-item self-rated true or false questionnaire to assess temperament.
17. Past Medication Response Structured Assessment - A structured history of past response to medications to be administered during screening.
18. PTSD Scale - 10 item scale created by Co-Principal Investigator, [name], to assess past history of trauma, to be administered during screening.

